#### Strategies for engagement

All groups will receive weekly text messages encouraging participants to carry out the weekly homework available in the interactive e-book and/or videos. Participants will be asked about the difficulties in carrying out the homework and instructed on how to overcome them.

#### Fidelity of intervention delivery

The interventions will be conducted by four physiotherapy students ([name], [name], [name], and [name]) from Universidade Estadual do Centro-Oeste (UNICENTRO/Brazil). The team will receive 30 h of training regarding the interventions before the beginning of the *EducaDor* programme. The chief researcher of the study ([name]), who has 18 years of physiotherapy experience, will audit the online interventions once every month. To maintain the fidelity of the intervention delivery, the researchers will follow a structured manual of the *EducaDor* programme. All synchronous meetings will be recorded for further evaluation of the implementation fidelity.

#### Physiotherapy-based care

All participants will receive physiotherapy-based care in one of the five physiotherapy centres accredited to SUS, according to the scheduling availability of the services. The physiotherapy-based care consists of 10 sessions, mainly based on exercises and electrophysical agents. Patients will be treated in an outpatient physiotherapy centre by independent therapists to minimize the possible preference bias of therapists.

### Implementation strategies

The implementation strategies of the *EducaDor* programme have been developed alongside municipal health managers. Potentialities, barriers and solutions to promote the implementation of the *EducaDor* programme were discussed with health managers. Other ones were discussed with the research group to reorganise the operationalisation of the study phases (Table 2).

**Table 2 Tab2:** Potentialities, barriers and solutions to promote the implementation of the *EducaDor* programme

**Implementation domains**	Facilitators	Barriers	Solutions
**Intervention characteristics**	Stakeholders' perceptions of the quality and validity of evidence support the belief that the intervention will have desired outcomes and perception of the advantage of implementing the intervention and its adaptability to meet local needs The interventions can be tested and can reverse the implementation if warranted	(1) Difficulty of implementation in primary healthcare (2) Costs of the intervention and costs associated with implementation	(1) Implementation of interventions in the secondary level of healthcare (2) Low-cost interventions, PPSUS resources, and implementation of interventions in partnership with universities^a^ through research and extension projects
**Outer setting**	The public health organisation recognizes the high prevalence of chronic pain among SUS users by the number of requests for physiotherapy based-care for chronic pain treatment regulated by the municipality Also recognizes the evidence about the use of pain science education in chronic pain treatment, but this intervention is not yet available for SUS’s users in the municipality With the COVID-19 pandemic, the public health organisation of Guarapuava city could identify that most SUS users have smartphones and the internet, which can become these online interventions possible to occur There is a high network between public health organisations and the University (intervention providers)	(1) Currently, the public health organisation of Guarapuava city is not able to offer pain science education for SUS users in primary healthcare (2) Although the SUS’s users have access to smartphones and the internet, the stakeholders identified that the SUS’s users change their telephone numbers frequently (3) There is no pay-for-performance	(1) Implementation of the intervention in partnership with Unicentro, through the Clinical School of Physiotherapy, which is accredited to the secondary level of healthcare (2) Explain the importance of maintaining the telephone number over time; request home visits from community health agents to update the register (3) For the maintenance of the intervention after the study, we will request an increase in the number of service quotas to the Clinical School of Physiotherapy from the Health Department of the State of Paraná
**Inner setting**	The stakeholders agree that the intervention proposed is aligned with the norms, values and perceived risks and needs of the health policies They shared the perception of the importance of implementing the intervention and an online programme fit with the existing workflows and system in the municipality's health department considering the social distance imposed by the COVID-19 pandemic and the in-person return of other repressed care during the period of the pandemic Formal communication within the organisation for the referral of SUS’s users from primary healthcare to specialized healthcare (that is, to the secondary level of healthcare) is done through the information and technology system acquired by the municipal health department	(1) How to refer SUS users with chronic pain from primary healthcare to the *EducaDor* Programme (2) Health professionals' lack of knowledge about the new intervention in the digital information and communication system	(1) Provide referral access to the intervention in the digital information and communication system (2) Create a highlight on the intervention icon in the digital information and communication system, and insert video and explanatory text about the *EducaDor* programme; disseminate the video and text on the smartphones of health professionals in primary healthcare
**Characteristics of individuals**	The municipal health department organized study groups in various health thematic areas (eg, chronic diseases, elderly health, women's health, child and adolescent health, and others). Each study group is coordinated by a case manager, who organizes meetings with health agents, health professionals and municipal managers to discuss health cases and promote lectures to encourage continuing education. The study groups share about the health process in the respective primary healthcare unit, challenges and achievements. The case manager assists the team's engagement in strategic actions of municipal public health and represents a formal influence in the organisation on the attitudes and beliefs of colleagues about the interventions proposed for implementation. This relationship between public servants and managers can facilitate the relationship between them and SUS users, increasing the degree of commitment to public health	(1) Non-reference of SUS users with chronic pain to *EducaDor* programme due to lack of knowledge of health professionals about evidence-based practice	(1) Understand how evidence-based practice in primary healthcare is developed, specifically referring to *EducaDor* programme; explaining about pain science education and our programme to each case manager; participate in the study groups with the focus on chronic pain; disseminate the intervention to each primary healthcare unit leader
**Process of implementation**	Case managers and their study groups could facilitate the dissemination of adequate information at the various organisational levels of municipal public health and can assist in the process of implementing the *EducaDor* programme	(1) Lack of knowledge about pain science education on the part of physiotherapists who will be conducting physiotherapy-based care may discourage users from continuing the intervention	(1) Explain pain science education and our programme in-person to each physiotherapy centre accredited to the secondary level of healthcare

*SUS* Brazilian Unified Health System, *PPSUS* Research programme for SUS

^a^Universidade Estadual do Centro-Oeste (UNICENTRO): responsible for carrying out the interventions; e Universidade Cidade de São Paulo (UNICID): monitoring and guidance for the implementation process

The implementation process will be monthly monitored and evaluated on barriers and facilitators allowing adaptations throughout the implementation process of the *EducaDor* programme.

### Data management and statistical analysis

#### Data management

All data and materials will be used only for analysis of the present study and will be protected from any unnecessary exposure. The informed consent form will be digitally authenticated by researchers and patients. The recorded synchronous online meetings and audio from qualitative interviews will be available to the researchers only, and stored following the Brazilian General Law for Protection of Personal Data (LGPD). All data will be available for review and confirmation of data analysis when requested in the review process of publication without identifying the participants.

#### Sample size estimation

The sample size was estimated by simulation [61, 62]. The sample size simulation was performed in four steps: (1) defining the sample size problem and outcomes; (2) defining, writing and running the sample size simulation algorithm; (3) estimating the possible outcomes derived from the simulations; (4) finding the optimal sample size.

In step 1, the sample size problem was developed considering the following objective: to estimate the minimum sample size required to comply with a maximal type I error (*α*) of 0.05 or 5% and a maximal type II error (*β*) of 0.20 or 20%. The input outcomes were: populational mean pain intensity (0–10) of 6.0 with a standard deviation (SD) of 2.3; a hypothesised minimal clinically important difference (MCID) in pain intensity between groups of -1.0 with an SD of 0.25 [63]; three groups; three repeated measurements (baseline, 10 weeks and 6 months); a correlation within the repeated measurements of 0.30 or 30% [64]; a minimum of 30 participants per cluster (five physiotherapy facilities); a correlation within clusters of 0.20 or 20% [65]; and a loss to follow-up of 30% [66].

In step 2, the simulation algorithm was defined and written in R language [67]. The input outcomes defined in step 1 were then included in the algorithm. Normal distributions were simulated using the input means and SDs set in step 1 as hyperparameters. The simulations were gathered running the distributions considering several possible sample sizes for one group ranging from 5 to 5000 in 32 steps (i.e., 5 to 50 by 5; 60 to 100 by 10; 150 to 500 by 50; 600 to 1000 by 100; and 2000 to 5000 by 1000), with 100 replications for each step, and repeating this procedure 10 times (i.e., 10 iterations), summing up 32,000 sample size simulations in total.

In step 3, we estimated summary statistics for the simulated distributions in each of the 32 possible sample sizes, including the probability of type I error (*α*), type II error (*β*) and power (1-*β*). In step 4 we found the minimum sample size required to achieve the pre-defined type I error (*α* ≤ 0.05 or 5%), type II error (*β* ≤ 0.20 or 20%) and power (≥ 0.80 or 80%). At this moment the suggested minimum sample size was 80 participants per group. Then, corrections for loss to follow-up and correlations amongst the five clusters (physiotherapy facilities) and repeated measurements were applied [64, 65]. The sample size simulation suggested a minimum sample size of 105 participants per group, that is, 315 participants (105 in each treatment group) in total for this study.

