#### Quantitative data analysis

For continuous variables, we will calculate statistics of central tendency and dispersion, such as means and, standard deviation. For categorical variables, we will describe frequencies and absolute numbers. Normality will be investigated by visual inspection of histograms. The baseline characteristics of the participants and implementation outcomes will be calculated using descriptive statistics. The differences between groups and the 95% confidence interval will be calculated using mixed models. The fixed effect term will be composed of dummy variables indicating groups, and follow-up time-points, that is, 10 weeks and 6 months after baseline, and the interaction terms composed of group and time. The estimates will be adjusted for any potential differences that might exist at the baseline. The random effect term will be composed of: (1) a correlated random intercept and slope varying the intercept for the five physiotherapy clusters and varying the slope for time points; and (2) a correlated random intercept and slope varying the intercept for repeated measurements within each cluster and varying the slope for time-points [69].

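### The step from 80 to 105 per arm does not follow from the corrections the article lists, and the 5% error is not tied to any contrast or visit

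*Protocol article*

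**What the plan says.** Under Sample size estimation, the Protocol article sets the aim "to estimate the minimum sample size required to comply with a maximal type I error" of 5% and a type II error of 20%. The inputs are:

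- mean pain 6.0 with SD 2.3
- a between-group difference of -1.0, itself with an SD of 0.25
- three groups and three measurements, with correlation 0.30 between measurements
- five centres with at least 30 participants each and a within-centre correlation of 0.20
- "and a loss to follow-up of 30" per cent

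The simulation is reported in two stages. Before corrections: "At this moment the suggested minimum sample size was 80 participants per group". Loss, centre correlation and repeated measurements are then said to have been corrected for, with no formula shown, and the result is given as: "The sample size simulation suggested a minimum sample size of 105 participants per group, that is, 315 participants (105 in each treatment group"). The criterion throughout is "power (≥ 0.80 or 80" per cent.

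Under Quantitative data analysis, "The differences between groups and the 95% confidence interval will be calculated using mixed models", with fixed effects for group, the two follow-up times "and the interaction terms composed of group and time", adjustment for baseline differences, and random effects for centre. Under Procedures and randomisation, individuals are randomised in blocks stratified by centre. Current pain intensity is the primary effectiveness outcome, measured at baseline, 10 weeks and 6 months. No primary follow-up visit is named for it.

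**The concern.** Three corrections are said to take 80 to 105, yet the loss correction alone, done in the usual way, already goes past 105. Either some corrections reduced the number or one of them was left out or done differently. The article does not say which.

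This matters because the 80% power and the maximal 5% error are the two properties by which readers will judge the pain comparisons. If power was lower than stated, a null difference between two delivery modes could be over-read as similarity. If 5% applies to each of several contrasts, one nominally significant difference could be over-read as a controlled finding.

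**Working it through.** **Inputs.** All come from Sample size estimation: difference 1.0, SD 2.3, effect SD 0.25, correlation between measurements 0.30, within-centre correlation 0.20, loss 30%, 80 before and 105 after corrections. The article does not state sidedness. I assume two-sided 5%, in line with the planned 95% intervals.

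**1. The figure of 80.** A two-sample t-test (noncentral t) gives 78.0% power at 80 per arm and first passes 80% at 85. A three-group F test with one arm differing by 1.0 gives 75.5% at 70 and 81.4% at 80. The search grid moved in tens in this range, with 1,000 simulations per size, so the Monte Carlo standard error is sqrt(0.8 × 0.2/1000) = 1.3 points. On that grid 80 is a reasonable answer, and I make no point of it.

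**2. From 80 to 105.**

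| Corrections used | Calculation | Per arm |
|---|---|---|
| Loss, as n/(1−d) | 80/0.70 | 114.3, so 115 |
| Loss, as n×(1+d) | 80 × 1.30 | 104 |
| Loss and baseline correlation | 80 × (1 − 0.30²)/0.70 = 80 × 0.91/0.70 | 104 |
| Loss, baseline correlation and centre as a stratification gain | 80 × 0.91 × 0.80/0.70 | 83.2 |

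Both routes to 104 omit the centre correlation. A product with three factors that comes close is 80 × 1.30 × 1.8 × 0.56 = 104.8. There, 1.8 = 1 + (5 − 1) × 0.20 uses the number of centres as if it were the cluster size, and 0.56 = (1 + 0.30)/2 − 0.30². Neither the loss factor nor the cluster factor in that product is valid.

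**3. Evaluable participants.** 105 × 0.70 = 73.5 per arm.

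**4. Pairwise power at 73.5 per arm.** The standard error of a difference is SD × sqrt(2/73.5). The SD is multiplied by sqrt(0.91) when baseline pain is a covariate, and by sqrt(0.80) when a 20% between-centre share of variance is removed. The last column averages power over a normal effect with mean 1.0 and SD 0.25.

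| Analysis | SE | Power at 1.0 | Averaged |
|---|---|---|---|
| Unadjusted | 0.379 | 74.5% | 71% |
| Baseline | 0.362 | 78.4% | 74% |
| Centre | 0.339 | 83% | 78% |
| Baseline and centre | 0.324 | 87% | 81% |

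**5. Type I error.** With three equal arms, each pair tested at two-sided 5% and no adjustment, simulation (400,000 draws) gives at least one false positive in about 12% of trials at one visit. Over two visits with correlation 0.30 between them, the figure is about 22%.

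**The case against.** The strongest reply is that 80 is a pre-correction figure, so it should not be set directly against a post-loss count. With the plan's own correlation of 0.30, the evaluable minimum becomes 80 × 0.91 = 72.8, which 73.5 meets. Power of 78.4% at 73.5 with baseline adjustment equals the 78.0% at 80 without it. The planned model also includes centre, which can take power to 83–87%. This reply stands, and it limits the conclusion. It does not explain where the centre correction went: crediting it as well gives about 83 per arm, not 105.

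A reader might infer four stronger things, which the article does not support.

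- **That 80% power is not delivered.** This depends on whether centre variance is removed and on whether the effect SD is averaged over.
- **That loss was inflated by the 80 × 1.30 mistake.** This is plausible, but 80 × 0.91/0.70 fits equally well, and the text cannot separate the two.
- **That a cluster design effect of 1 + 29 × 0.20 = 6.8 applies, giving 80 × 6.8/0.70 = 777 per arm.** Individuals are randomised within centres, so it does not apply.
- **That no set of corrections can reach 105.** The 104.8 product above shows otherwise, although its factors are unsound.

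On error control, the article never says that 5% belongs to a single contrast. An omnibus test would also explain 80, and a multiplicity rule may be in an analysis plan that is not shown. That is fair. But the analysis section names no omnibus test, and the sample size section sets "a maximal type I error (*α*) of 0.05 or 5" per cent without saying what it covers.

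**Conclusion.** The point holds in a limited form. The article's account of how 80 became 105 does not reproduce with sound versions of all three corrections, and the simple routes to 104 leave out the 0.20 centre correlation. With about 73 evaluable per arm, pairwise power lies between about 75% and 87% at a fixed 1.0-point difference, and between about 71% and 81% averaged over the stated effect SD. Which figure applies depends on how far baseline and centre adjustment are credited. The maximal 5% error has no stated contrast or visit, against a familywise rate of about 12% (three contrasts, one visit) or 22% (six contrasts) if nothing is adjusted.

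These figures assume two-sided tests, equal arms, 30% loss in each arm, no information from participants who are lost, baseline adjustment that uses pain as a covariate with correlation 0.30, and a true between-centre share of 0.20.

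**What to change.** Keep 315 participants and make three changes.

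1. Replace the step from 80 to 105 with a calculation that shows how loss, centre and baseline correlation each enter. State about 73 evaluable per arm and the power for one pairwise 1.0-point difference, two-sided 5%, under the planned model adjusted for baseline and centre. Say whether the effect SD of 0.25 is averaged over.
2. Name one primary visit for pain. Six months is a natural candidate, because the cost-effectiveness analysis already uses pain at that visit.
3. At that visit, test the three pairwise contrasts only if the 2-degree-of-freedom test of arm is significant. With three arms this holds 5% without splitting alpha. If all arms are equal, the first test limits the error. If only one pair is equal, only one true null remains. Report the other visit as supportive.

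The cost is rewording. The stated power may become slightly less favourable and pairwise claims slightly stricter.

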### Procedures and randomisation

Individuals referred to the EducaDor programme will first be contacted by a researcher ([name]; [name]) via an electronic videoconferencing system at the scheduled consultation. During this initial contact, the researcher will screen the participant for eligibility and provide information about the EducaDor programme, as well as the name of the referred physiotherapy centre. Eligible participants will receive a link to an online consent form via email or text message, which they can accept to participate. Once the consent form is accepted, one researcher will conduct the baseline assessment, and another researcher will randomly assign the participant to one of the intervention groups.

Participants included in the study will receive physiotherapy-based care and the *EducaDor* programme as per randomisation into three different modes of delivery: (1) synchronous online group; (2) asynchronous videos group; or (3) interactive e-book group. Although the three groups have the interactive e-book, the synchronous online group and the asynchronous videos group receive additional types of digital content that are accessible to participants who cannot read and/or write in Portuguese. Then, the first step of randomisation will be done for participants who cannot read and/or write in Portuguese into (1) synchronous online group or (2) asynchronous videos group. The second step of randomisation will include all other eligible participants into the three different modes of delivery: (1) synchronous online group; (2) asynchronous videos group; or (3) interactive e-book group.

One researcher ([name]) will perform a stratified block randomization within the five physiotherapy centres accredited at SUS in the city, at the ratio of 1:1, using Excel software. The randomised list will be under the custody and confidentiality of the researcher ([name]). One week before the start of the *EducaDor* programme, one researcher ([name]) will send a list of participants to the researchers responsible for the interventions ([name], [name], [name], and [name]). The intervention researchers will then contact the participants to explain the intervention according to group allocation.

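### At a total of 315 with equal allocation in each step, the two-step randomisation gives 105 per arm only if no non-reader enrols; otherwise the e-book arm is expected to be smaller

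*Protocol article*

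**What the plan says.** **Size.** Protocol article, Sample size estimation: the trial is sized with "three groups; three repeated measurements (baseline, 10 weeks and 6 months" among its inputs. The target is a type I error "of 0.05 or 5% and a maximal type II error" of 20%, that is "power (≥ 0.80 or 80"%. The outcome is a "populational mean pain intensity (0–10) of 6.0 with a standard deviation (SD) of 2.3", with a hypothesised difference "in pain intensity between groups of -1.0 with an SD of 0.25". The simulation gives 80 per group. After corrections for loss to follow-up, clustering and repeated measurements, the result is "315 participants (105 in each treatment group) in total for this study", described as a minimum. No input concerns literacy or unequal arms.

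**Allocation.** Procedures and randomisation: "the first step of randomisation will be done for participants who cannot read and/or write in Portuguese into (1) synchronous online group or (2) asynchronous" (the latter being the video arm). A second step takes all other eligible participants into the three arms. The only ratio given is "at the ratio of 1:1, using Excel software", in blocks stratified by the five physiotherapy centres.

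**Who can enter.** Settings and eligibility criteria: participants must speak Portuguese. Reading and writing are not required, so the people for whom step 1 was built are eligible.

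**Analysis set.** Missing data: the main analysis takes all randomised participants.

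**The concern.** The size calculation treats the trial as three equal arms, but the allocation scheme has a stratum that can never enter the e-book arm. Each such person adds to the other two arms and, at a fixed total, takes a place from someone who might have entered the e-book arm. Two of the three pairwise comparisons involve that arm. The printed group size, and the single power figure attached to it, would therefore not describe those comparisons. The ratio of 1:1 does not settle the matter: it suits a two-arm step but does not say how the second step divides people over three arms.

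This is not a detail that a condensed article leaves to a fuller document. The article prints both the allocation scheme and the arm sizes, and the two do not agree.

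**Working it through.** **1. The plan's own figure.** Inputs from Sample size estimation: difference 1.0, SD 2.3, alpha 0.05, power 0.80. The article does not state sidedness, so two-sided is assumed. A two-sample t-test with 80 per group has power 78.0%, within two points of 80%, and the simulation grid moved in steps of 10 at this size. So 80 is accepted as the starting figure. The route from 80 to 105 is not shown: 80 × (1 − 0.30²) / 0.70 = 104 and 80 × 1.3 = 104 both come close. The check below takes 105 and 315 as given.

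**2. Expected arm sizes.** Let p be the share of the 315 who cannot read and/or write. Assume a fixed total and equal allocation within each step.

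- E-book: 315 × (1 − p)/3 = 105(1 − p)
- Each other arm: 315 × [(1 − p)/3 + p/2] = 105(1 + p/2)

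The total is 105(1 − p) + 2 × 105(1 + p/2) = 315, as it should be. For p = 10%: 105 × 0.90 = 94.5 and 105 × 1.05 = 110.25. The three arms are equal only at p = 0.

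**3. Power by contrast.** Two-sample t-test, two-sided 0.05, difference 1.0, SD 2.3, and the plan's 30% loss, so each arm is multiplied by 0.70. This is a simple stand-in for the planned mixed model. It is used for the change in power between rows, not for the level. The values of p are assumptions.

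| p | E-book / each other arm | E-book contrast, all randomised | E-book contrast, step-2 participants only | Synchronous vs video, all randomised |
|---|---|---|---|---|
| 0 | 105 / 105 | 74.5% | 74.5% | 74.5% |
| 5% | 99.8 / 107.6 | 73.9% | 72.3% | 75.5% |
| 10% | 94.5 / 110.3 | 73.1% | 69.9% | 76.5% |
| 15% | 89.3 / 112.9 | 72.3% | 67.4% | 77.5% |
| 20% | 84.0 / 115.5 | 71.2% | 64.7% | 78.5% |

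The step-2 column has 105(1 − p) in both arms compared, because only step-2 participants could have been assigned to any of the three arms.

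**4. Loss due to allocation alone** (each row against p = 0, differenced before rounding):

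- All randomised: 0.6, 1.3, 2.2 and 3.3 points.
- Step-2 participants only: 2.2, 4.6, 7.1 and 9.8 points.
- With the smaller SD 2.3 × √(1 − 0.30²) = 2.194, the step-2 figures are 78.4% at p = 0, then 76.2%, 74.0%, 71.5% and 68.8%. The losses are about 2, 4, 7 and 10 points.

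**5. Total needed for an expected 105 in the e-book arm.** 315/(1 − p): 332, 350, 371 and 394 at p = 5%, 10%, 15% and 20%.

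**The case against.** A reader might infer that the scheme cannot deliver 105 in the e-book arm. The article does not support that. The shortfall needs three conditions together: at least some non-readers enrol, the total stops at 315, and step 2 allocates equally. The article calls 105 per group a minimum, sets no explicit cap at 315 and never states the step-2 ratio. Recruiting on until the e-book arm reaches 105, or weighting step 2 towards it, would give 105. Neither is described, but neither is ruled out.

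A reader might also set the step-2 figures of about 65% to 76% against the stated 80% and conclude that the allocation removes that much power. That does not follow either. At p = 0 the same calculation already gives 74% to 78%. That gap comes from applying the 30% loss to 105 and is a separate matter. The restriction to step-2 participants is also not what the plan specifies. Under the all-randomised analysis the other arms grow as the e-book arm shrinks, and the allocation effect is small.

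Finally, p is unknown. Participants need an internet-connected device and must accept an online consent form, which may keep p low, although nothing in the article shows this. No e-book contrast is singled out as the powered comparison, and synchronous versus video gains.

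All of this stands as a limit on size. It does not reconcile the two sections. A separate randomisation step presupposes that non-readers will enrol, and the sample size section makes no allowance for them.

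**Conclusion.** The point holds as an inconsistency between Procedures and randomisation and Sample size estimation. With 315 in total and equal allocation within each step, 105 in every group is expected only if nobody uses step 1. Otherwise the e-book arm is below 105 and the other two are above it.

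The effect on power depends on an assumed p of 5% to 20%. It is modest under the planned all-randomised analysis, at about 0.6 to 3.3 points for the e-book contrasts. It is larger, at about 2 to 10 points, if those contrasts are limited to the people randomised among all three arms. One might prefer that restriction because pooling compares arms that differ in literacy by design, but that is a separate question. Since the contrasts move in opposite directions, one group size and one power figure cannot describe all three. The correction is worth making and does not call the design itself into question.

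**What to change.** In Procedures and randomisation, state the ratio for each step: 1:1 in step 1, and 1:1:1, or whatever weighting is intended, in step 2.

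In Sample size estimation:

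- Replace the equal group size with the expected arm sizes at 315, using a value of p taken from referral or screening data. With equal steps these are 105(1 − p) and 105(1 + p/2).
- Say whether 315 is fixed or whether recruitment continues until every arm reaches 105. If it continues, give the total, 315/(1 − p) in expectation.
- Restate power separately for the e-book contrasts and for synchronous versus video, and say which participants each figure rests on.

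The cost is wording in two sections, one short recalculation, and slightly less favourable stated figures for the e-book contrasts. If 315 is kept, no extra enrolment is needed, but the smaller e-book arm is then an acknowledged feature of the design. Keeping 105 as a true minimum in that arm would mean either more participants or a weighted second step.
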